#### Effects

To analyze the effects on the primary outcome (total neuropsychiatric symptoms), repeated measures MANOVA will be used to assess the group differences across time. The condition (intervention vs. control) is the independent variable and the outcome measures across the three measurements are the repeated dependent variables. Simple contrasts will be used post-hoc to compare the post-intervention and follow-up measures with the pre-intervention measures. Effect sizes at post-intervention and follow-up will be calculated as Cohen’s d. Effect sizes between .56 and 1.2 are interpreted as large, between .33 and .55 as moderate, and below .33 as small [53].

We will also tentatively study the effects of the intervention on the four clusters of neuropsychiatric symptoms (hyperactivity, psychosis, affective symptoms, and apathy). As these measures are often not normally distributed, we will use a dichotomized outcome (clinically relevant symptoms or not, based on a FxS score of 4 and higher) [43]. We will carry out four logistic regression analyses with condition (intervention versus control) and presence of clinically relevant symptoms within the respective clusters at baseline as independent variables and presence of clinically relevant symptoms at follow-up as dependent variable. The odds-ratios will be used to provide estimates of the effect sizes in terms of Cohen’s d.

For the secondary outcome measures, three repeated measures MANOVA’s will be conducted, similar to the analysis for the primary outcome. The effect sizes will be given in Cohen’s d.

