#### Sample size calculation

Based on systematic reviews [15, 17, 18], a small significant effect is expected for the primary outcome at follow-up. Hence, 74 participants are needed (GPower: f = 0.15; alpha = .05; power = .80; repeated measures anova with 2 groups and 3 measurement points; *r* = .50 between measurements). Given the vulnerability of the participants and a high mortality rate, we expect a drop-out of 30% [15, 17, 18]. Hence, 106 participants need to be included, 53 per condition.

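### The primary repeated measures MANOVA treats baseline NPI as a response; using it as a prespecified covariate would answer the same question with more power

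*Protocol article*

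**What the plan says.** Under Statistical analyses, Effects, the article states for the primary outcome that "repeated measures MANOVA will be used to assess the group differences across time". Condition is the independent variable. The NPI totals at T0, T1 and T2 are all dependent variables, so baseline is a response. It continues: "Simple contrasts will be used post-hoc to compare the post-intervention and follow-up measures with the pre-intervention measures". Cohen's d is promised at both later visits.

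The Sample size calculation section says that "a small significant effect is expected for the primary outcome at follow-up" and sizes the trial with "GPower: f = 0.15; alpha = .05; power = .80; repeated measures anova with 2 groups and 3 measurement points" and a correlation of .50 between measurements, concluding that "74 participants are needed". With 30% drop-out this becomes 106.

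Three other places bear on the point:
- In the same Effects section, the four symptom-cluster analyses already use baseline status as a covariate and follow-up status as the outcome.
- Randomization check allows adjustment for baseline variables only after a significant imbalance test and a further look at their relation to later outcomes.
- Missing values plans multiple imputation so that everyone randomised enters the analysis. Observed-data results serve only as a comparison.

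**The concern.** The group-by-time test asks whether the arms' profiles over T0, T1 and T2 differ in any way. It spends two degrees of freedom and, in effect, works on changes from baseline. Under randomisation the true baseline difference is zero, so treating T0 as a response estimates a quantity already known. As a covariate, the same measurement would remove variance instead.

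The omnibus test also does not locate the effect. A difference at T1 alone and a fully sustained difference of the same size give it the same power (shown in the working). The follow-up effect that the sample size section anticipates is therefore left to contrasts made after the omnibus test, and those use the noisier change score. Whether baseline NPI is ever adjusted for depends on the data, through the imbalance check, and is not fixed in advance.

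**Working it through.** **Inputs.** From Sample size calculation: f = 0.15, α = .05, power .80, 2 groups, 3 measurements, r = .50, N = 74 (37 per arm), 30% drop-out. Assumed, because the article does not give them: equal variances (σ² = 1), equal correlations, a two-sided .05 level for single contrasts, and the shape of the effect over T1 and T2.

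**The plan's own figure.** For the within-between interaction, λ = f²·N·m/(1−r) = 0.0225 × 74 × 3/0.5 = 9.99. With df 2 and 144, power is 80.6%. The multivariate version, df 2 and 71, gives 79.7%. The between-groups variant would need 236. Drop-out: 74/0.70 = 105.7, so 106. The stated figures reproduce, and only as the two-df group-by-time test.

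**Contrast at T2, d = 0.5.**
- Change score: variance 2(1−r) = 1.00. SE = √(1.00 × 4/74) = 0.2325, noncentrality 0.5/0.2325 = 2.15, df 72, power **56%**.
- Baseline-adjusted: variance 1−r² = 0.75. SE = √(0.75 × 4/74) = 0.2013, noncentrality 2.48, df 71, power **69%**.

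**Joint two-df test.** λ = (N/4)·δ′V⁻¹δ with δ = (d₁, d₂) at T1 and T2.
- Present MANOVA: V has variance 1.00 and covariance 1−r = 0.50, so δ′V⁻¹δ = (d₁² + d₂² − d₁d₂)/0.75, df 2 and 71.
- Baseline-adjusted: V has variance 0.75 and covariance r−r² = 0.25, so δ′V⁻¹δ = (0.75(d₁² + d₂²) − 0.5·d₁d₂)/0.5, df 2 and 70.

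| Shape | MANOVA λ | Power | Adjusted λ | Power |
|---|---|---|---|---|
| Sustained (0.5, 0.5) | 18.5 × 0.333 = 6.17 | 58% | 18.5 × 0.500 = 9.25 | 76% |
| Linear growth (0.25, 0.5) | 18.5 × 0.250 = 4.63 | 46% | 18.5 × 0.344 = 6.36 | 59% |

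The baseline-adjusted mean of T1 and T2 has 85% and 61% for these two shapes.

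**What f = 0.15 means by shape.** From f² = Σ(d_t − mean)²/12, a sustained effect has f² = d²/18, so d = 0.15 × √18 = 0.636. An effect of 0.636 at T1 and zero at T2 gives the same λ, so the omnibus power is 79.7% in both cases.

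**Single T2 contrast against the present omnibus test** (f = 0.15, r = .50, N = 74; MANOVA 80% throughout):

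| T2 effect as share of T1 | Adjusted T2 | Adjusted joint |
|---|---|---|
| 100% | 88% | 93% |
| 85% | 81% | 93% |
| 80% | 78% | 93% |
| 75% | 74% | 93% |
| 50% | 44% | 91% |

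With d fixed at 0.636 at T1 and half that at T2, the T2 contrast has 34%, the MANOVA 67% and the adjusted joint test 81%.

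**Sensitivity to r** (sustained d = 0.5). At r = .7, T2 contrast 84% against MANOVA 81%; at r = .8 both are 94%. The adjusted joint test has 89% and 97% at those values.

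**The case against.** The strongest reply is that nothing here is an error. The trial is sized on a repeated measures test and analysed with the matching multivariate test, and the numbers agree. That stands.

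The reply also corrects several stronger readings that a reader might reach.
- *That T2 is the sole target.* This rests on one phrase in Sample size calculation. The primary objective, at the end of the Background, names no time point, and Effects reports Cohen's d at both visits. Naming T2 follows the sample size text, but it remains the sponsor's choice.
- *That a T2 contrast always has more power than the MANOVA.* It does not if the effect fades. Fading is plausible: volunteer visits end within 8–10 weeks and the printed book arrives at about 3 months, although continued use is advised.
- *That the MANOVA drops everyone with a missed visit.* Missing values plans multiple imputation for the main analysis, so this applies only to the observed-data comparison.
- *That post-hoc means unplanned, or that the omnibus test is at fault for lacking direction.* The contrasts are named in advance and will show the sign and timing of any effect. A two-sided T2 contrast has no direction either.

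The powers above use 74 analysed, the plan's own figure. They set the tests side by side at a common size and do not forecast the power of the imputed analysis of 106.

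None of this answers the narrower point: for the same question, joint or at T2, baseline NPI does more as a covariate than as a response.

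**Conclusion.** The point holds as one of efficiency and alignment. The planned test is valid and 74 and 106 are arithmetically right; the documents do not support calling the analysis or the sample size wrong.

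Like for like, covariate adjustment had higher power for every effect shape and correlation examined in which there was an effect to detect. At r = .50 and d = 0.5 the gain is about 12 percentage points for the T2 contrast and 14 to 19 for the joint test. These sizes assume equal variances and correlations and the stated r, and they shrink as r rises.

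Replacing the omnibus test by T2 alone is a separate decision and a genuine trade-off. It gains power only if the T2 effect is at least roughly 80–85% of the T1 effect at r = .50, and for a sustained effect it gains little at r = .7–.8. Its main merit is that it tests the effect where the sample size section expects it.

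**What to change.** In the primary model, take NPI total at T1 and T2 as responses and baseline NPI as a covariate fixed in advance, whatever the randomisation check shows. A mixed model with visit-by-arm terms and unstructured covariance would serve, as would ANCOVA, run within the planned multiple imputation where needed. Report baseline-adjusted differences at T1 and T2 with 95% CIs, and derive Cohen's d from them.

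State the primary contrast. Since the sample size text points to follow-up, name T2 as primary and T1 as secondary. If the sponsor means both visits, use the baseline-adjusted joint test or the adjusted mean of T1 and T2. The joint test holds up better when the effect is confined to one visit: for d = 0.636 at one visit only it has 84%, against 48% for the mean. The MANOVA can stay as a sensitivity analysis.

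Cost: no new data. The analysis text changes, and the sample size basis must be restated for the new test. A T2-only primary loses power if the effect fades. The choice should be fixed before outcome data are analysed.

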#### Primary outcome

##### Neuropsychiatric symptoms (NPS)

To assess the effect of the intervention on the primary outcome, neuropsychiatric symptoms, the Neuropsychiatric Inventory (NPI) will be used at all three time points in all participants. The NPI is a reliable and valid measure that is filled out by the primary informal caregiver [41]. The NPI is often used to measure neuropsychiatric symptoms, also in pharmacological and psychosocial intervention studies. The instrument is developed by Cummings (1994) and translated in Dutch by De Jonghe, Borkend and Kat (1997) [42]. The NPI measures the frequency, severity and distress of twelve neuropsychiatric symptoms (Delusions, Hallucinations, Agitation/Aggression, Depression/Dysphoria, Anxiety, Elation/Euphoria, Apathy/Indifference, Disinhibition, Irritability/Lability, Aberrant motor behavior, Sleep and Nighttime Behavior Disorders, and Appetite and Eating Disorders). The frequency (F) is provided on a scale from 0 = never to 4 = daily, the severity (S) on a scale from 0 = not to 3 = severe. The score for each of the twelve symptoms is computed as the frequency multiplied by the severity, resulting in a score ranging from 0 to 12. An FxE score of 4 or higher is seen as clinically relevant symptoms. The twelve FxE scores are added to a total score (0-144) or to four scores of symptom clusters: hyperactivity, psychosis, affective symptoms, and apathy [43].

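### The four NPI cluster outcomes are cut to yes/no because they are non-normal, which does not require a cut; an ordinal analysis of the full scores should stand beside the logistic models

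*Protocol article*

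**What the plan says.** The protocol article, under Neuropsychiatric symptoms (NPS), defines each symptom score as "computed as the frequency multiplied by the severity, resulting in a score ranging from 0 to 12". It then attaches the clinical cut to that score: "An FxE score of 4 or higher is seen as clinically relevant symptoms". The twelve symptom scores can be added to a total or to four cluster scores.

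Under Effects, the clusters are introduced with the words "We will also tentatively study the effects of the intervention on the four clusters of neuropsychiatric symptoms". The reason for the yes/no outcome is distributional: "As these measures are often not normally distributed, we will use a dichotomized outcome". The outcome is defined as "clinically relevant symptoms or not, based on a FxS score of 4 and higher". Four logistic regressions follow, one per cluster. Besides condition they take "presence of clinically relevant symptoms within the respective clusters at baseline as independent variables", and they model "presence of clinically relevant symptoms at follow-up as dependent variable". The odds ratios are then converted to Cohen's d. The article describes no analysis of the cluster scores on their full scale.

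**The concern.** Non-normality rules out a plain normal-theory model at most. It does not lead to two categories. A proportional-odds model makes no normality assumption, uses only the order of the scores, and yields an odds ratio that can be converted to d as already planned.

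The cut discards graded information at both time points. If one symptom determines a participant's status, a fall from 12 to 4 leaves that status unchanged, while a fall from 4 to 3 counts as resolution. The clusters are the only place where the trial asks which kinds of symptom respond, and the sample is small. If the intervention lowers scores across their range, the planned models could miss an effect that the collected data contain.

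**Working it through.** **1. The plan's own figure.** Inputs from Sample size calculation: f = 0.15, alpha .05, power .80, 2 groups, m = 3 measurements, correlation .50, drop-out 30%. For the within-between interaction:

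- λ = f²·N·m/(1 − ρ) = 0.0225 × 74 × 3 / 0.5 = 9.99, with df 2 and 2 × (74 − 2) = 144.
- The noncentral F distribution gives power .806 at N = 74 and .795 at N = 72, so 74 is the smallest even total.
- 74 / 0.70 = 105.7, hence 106, or 53 per arm.

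Both stated numbers reproduce, but they concern the NPI total score. No power is stated for the clusters. Those analyses will have about 37 per arm if the expected drop-out occurs, and at most 53 per arm with imputation of all randomised participants.

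**2. Effect size.** None is given for a cluster. Reading f = 0.15 as d = 2f gives d = 0.30. Read as an interaction, d at T2 equals 0.15/√(mean v²), where v is half the relative group difference at each visit, centred.

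- Effect complete by T1 and held: v = (−1/3, 1/6, 1/6), √(mean v²) = 0.236, d = 0.64.
- Linear effect: v = (−1/4, 0, 1/4), √(mean v²) = 0.204, d = 0.73.

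The main range below is d = 0.30 to 0.50.

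**3. Broad shift of scores.** Assumptions: latent normal baseline and follow-up correlated .50; follow-up shifted by d; values cut to the attainable symptom scores 0, 1, 2, 3, 4, 6, 8, 9, 12; 800 runs per row. The planned logistic model (binary outcome, binary baseline) is compared with a proportional-odds (PO) model (ordinal outcome, baseline score). Gaps are percentage points, taken before rounding.

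| Per arm | d | Share at 4 or more | Logistic | PO | Gap |
|---|---|---|---|---|---|
| 37 | 0.30 | 50% | .191 | .305 | 11.4 |
| 37 | 0.30 | 30% | .144 | .258 | 11.4 |
| 37 | 0.30 | 20% | .125 | .220 | 9.5 |
| 37 | 0.50 | 50% | .411 | .624 | 21.3 |
| 37 | 0.50 | 30% | .331 | .556 | 22.5 |
| 37 | 0.50 | 20% | .179 | .449 | 27.0 |
| 53 | 0.30 | 50% | .250 | .393 | 14.3 |
| 53 | 0.30 | 30% | .204 | .335 | 13.1 |
| 53 | 0.30 | 20% | .158 | .282 | 12.5 |
| 53 | 0.50 | 50% | .541 | .771 | 23.0 |
| 53 | 0.50 | 30% | .415 | .682 | 26.8 |
| 53 | 0.50 | 20% | .346 | .586 | 24.0 |

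The Monte Carlo standard error of one power is at most √(0.25/800) = 0.018. A second run (1,000 per setting) gave gaps of 8.9, 7.8 and 11.2 for the first three rows. At d = 0.64 the gaps were 16 to 39 points.

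With no effect and 37 per arm, rejection rates for shares of 50, 30 and 20% were .042, .061 and .038 (logistic) and .040, .059 and .050 (PO), so the gain is not bought with type I error. With 10% at or above the cut, logistic power at d = 0.30 to 0.50 was only .02 to .11. Its null rejection rate there was .010 (37 per arm), so that setting is left out of the range.

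Almost all of the gap comes from cutting the outcome. Replacing the baseline score by its yes/no version in the PO model changed power by about 4 points at most (for example .305 to .292, and .624 to .585).

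**4. Other effect shapes.** Here the full-score comparator was rank ANCOVA. In a small check (60 trials), PO gave power .72 and .85 where rank ANCOVA gave .66 and .82.

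- Latent shift: the full-score analysis gained about 5 to 24 points (600 runs per setting).
- Symptoms resolving to zero: it gained about 9 to 32 points.
- Scores shrinking proportionally: the logistic model won by about 5 to 22 points.
- Treatment moving each symptom at 4 or more down to 1–3 only (N = 74, correlation 0.6, 1,000 runs; 2, 3 and 4 symptoms per cluster): with probability 0.4, logistic .18, .19, .22 against .07, .10, .11; with probability 0.6, .35, .50, .46 against .07, .13, .18.

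The direction of the difference therefore depends on the effect shape.

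**The case against.** The strongest reply is that the cut is clinical as well as distributional. The protocol defines 4 or more as clinically relevant and cites a source for it. On that definition a participant who falls from 12 to 4 still has a relevant symptom, so counting no change is what the outcome means. A proportional-odds model answers a different question, whether scores tend to be lower. This stands, and it is why the logistic model should be kept.

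Second, the power advantage is not general. It assumes a shift across the score or full resolution, and it reverses for effects concentrated at the cut. This also stands. At d = 0.30 and 37 per arm, moreover, both analyses are weak (.13 to .19 against .22 to .31).

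Third, the stakes are low. The clusters are studied tentatively, they are not among the stated objectives, and Table 1 names only the NPI total as primary, which is analysed undichotomised. This limits severity, but it does not make non-normality a reason for a cut.

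A reader might also infer that the per-symptom cut is wrongly applied to cluster sums, so that four symptoms scoring 1 each would count as relevant. The text does not support that as an error. The phrase about symptoms within the respective clusters more naturally means any one symptom at 4 or more. It would only help to say so outright.

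**Conclusion.** The point holds in a limited form. The one reason given for dichotomising does not require it, both outcome and baseline covariate are cut, and no full-score cluster analysis is planned.

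If the intervention shifts scores broadly or resolves symptoms, the planned models give up roughly 5 to 30 points of power at 37 to 53 per arm. That range rests on assumed prevalences, correlations and effects, because the article gives no cluster prevalence, cluster effect size or effect shape. If the effect lies mainly at the cut, or is a proportional reduction, the logistic model can be the stronger one.

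A reader might infer a fixed loss, or conclude that the yes/no analysis should be dropped. Neither follows from the documents. This is a worthwhile refinement of an exploratory analysis and does not touch the primary conclusion.

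**What to change.** In the Effects section, for each cluster:

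- Analyse the T2 cluster score (sum of frequency × severity) by proportional-odds regression on condition and the baseline cluster score. Keep the planned conversion of the odds ratio to Cohen's d.
- Retain the logistic model as the clinical-threshold companion. Define the outcome explicitly as any symptom in the cluster scoring 4 or more, and adjust for the baseline cluster score instead of its yes/no version.
- Replace the distributional justification for the cut by the clinical one.

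The cost is one paragraph of wording and no new data. The downsides are one more exploratory model per cluster (four in all) and a proportional-odds assumption to check. The new odds ratio also refers to a higher score, not to the clinical threshold, so the two results must be labelled as answers to different questions.

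### The tentative symptom-cluster models need a fit that stays finite in sparse clusters, and their Cohen's d should not be read against the bands set for the NPI total

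*Protocol article*

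**What the plan says.** The Effects part of the statistical analyses section introduces the cluster analysis as tentative. Each cluster is reduced to a yes/no outcome. The model is described as follows: "We will carry out four logistic regression analyses with condition (intervention versus control) and presence of clinically relevant symptoms within the respective clusters at baseline" are the independent variables, and presence at follow-up is the dependent variable. The conversion is then fixed: "The odds-ratios will be used to provide estimates of the effect sizes in terms of Cohen" (the sentence ends with 's d).

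One paragraph earlier, for the NPI total, the article sets bands for reading d: "Effect sizes between .56 and 1.2 are interpreted as large, between .33 and .55 as moderate, and below .33 as small". The cluster paragraph does not repeat them, but it uses the same name for the effect size.

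The Missing values part plans five imputed data sets covering everyone randomised, and a comparison with the observed data only. No estimator, conversion formula or cluster prevalence is given.

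**The concern.** Two features of the plan matter together: a yes/no outcome in a small sample, and a summary that needs a finite odds ratio.

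- **Sparse clusters.** If no one in an arm has clinically relevant symptoms in a cluster at follow-up, unpenalised maximum likelihood has no finite solution for the condition effect. Software then either fails or prints an arbitrary large number. Pooling averages five log odds ratios, so a single non-finite one makes the average unusable.
- **Scale of d.** A d converted from an odds ratio adjusted for baseline presence is not the same quantity as a d from a difference in NPI means. With one label for both, a reader will naturally apply the bands from the paragraph above.

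At stake is the description of which symptom clusters respond to the intervention. The primary conclusion is not affected.

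**Working it through.** **Inputs.** The Sample size calculation section gives "GPower: f = 0.15; alpha = .05; power = .80; repeated measures anova with 2 groups and 3 measurement points", with r = .50. It continues "Hence, 74 participants are needed" and "we expect a drop-out of 30" per cent, leading to 106 participants, 53 per condition. Assumed here because the article gives no figure: control prevalence of a cluster at follow-up (5% to 50%), and the conversion d = ln(OR) × √3/π.

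**Step 1: reproduce the plan's sample size.** For the within-between interaction, λ = f² × N × m / (1 − ρ) = 0.0225 × 74 × 3 / 0.5 = 9.99 on 2 and 144 degrees of freedom. Power is 0.806, so 74 is reproduced. Then 74 / 0.70 = 105.7, rounded up to 106. The cluster models therefore use about 37 per arm in the observed data and 53 per arm in the imputed data. The design effect f = .15 corresponds to d = 2f = .30, which is used below as the true benefit.

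**Step 2: chance that an arm has no cases.** Let p be control prevalence. A benefit of .30 on an underlying normal score gives intervention prevalence q = Φ(Φ⁻¹(p) − .30). Then P = 1 − [1 − (1 − p)ⁿ] × [1 − (1 − q)ⁿ].

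Example with p = .10 and n = 37: q = .0569; .90³⁷ = .020; .9431³⁷ = .115; P = 1 − .980 × .885 = .13.

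| Control prevalence | 37 per arm | 53 per arm |
|---|---|---|
| 5% | 47% | 30% |
| 10% | 13% | 4.8% |
| 15% | 3.2% | 0.7% |
| 20% | 0.7% | 0.1% |

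With no effect (equal prevalence) the risk is lower: 28%, 4.0% and 0.5% at 5%, 10% and 15% with 37 per arm, and 13%, 0.8% and 0.04% with 53 per arm.

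**Step 3: small-sample bias where estimates are finite.** In simulated trials with a true conditional d of .30 and prevalence 20% to 50%, unpenalised estimates averaged .31 to .34. That is an excess of about .01 to .035 beside a sampling SD of .23 to .47. With no true effect there was no systematic excess. At 5% prevalence the finite estimates averaged .22 to .30, so they were not inflated; the difficulty there is that many estimates do not exist. Firth's estimate averaged .29 to .31 at prevalence 10% or more and .24 to .28 at 5%, and was always finite.

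**Step 4: does penalisation still help when arms are not empty?** With 37 per arm and r = .50, the root mean squared error of d fell from .35 to .32 at 30% prevalence. At 20% the gain depends on how trials without a converged estimate are treated: from .49 to .39 in one simulation, and from .42 to .37 when trials with an empty arm or a non-converged coefficient are left out. Gains at 53 per arm are similar in direction.

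**Step 5: scale of the converted d.** Large-sample values for a latent d of .30 at the plan's r = .50:

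| Prevalence | From baseline-adjusted OR | From whole-sample OR |
|---|---|---|
| 10% | .357 | .337 |
| 20% | .326 | .299 |
| 30% | .311 | .281 |
| 50% | .298 | .265 |

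The same underlying effect gives an adjusted d between .298 and .357 according to prevalence alone, which is enough to fall on either side of .33. At an assumed r = .70 the adjusted values are .35 to .40.

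**The case against.** The strongest case against acting has four parts.

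- **The estimator is not named.** The article does not say the models are unpenalised, and a full analysis plan may settle it. This stands, so the point is conditional on the usual fitting method.
- **Sparse clusters may not occur.** The Background section lists delusions, agitation, aberrant motor behavior and apathy as the most common symptoms. Empty arms matter only at about 10% prevalence or below. The article neither states nor excludes such prevalence in people with very mild or mild dementia. This stands as a limit on size.
- **The analysis is tentative.** The clusters are neither the primary outcome nor a listed secondary outcome. This stands and keeps the point minor.
- **Baseline adjustment is sound.** Agreed, and it should be kept.

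A reader might go further and infer that the plan generally overstates d, so that small effects would often be labelled large. The documents do not support that. At the plan's own r = .50 the adjusted odds ratio returns .311 to .298 at prevalence 30% to 50% for a true .30, which is close. The article sets its bands in the NPI-total paragraph and does not say that they apply to clusters. Most large labels in a trial of this size would be sampling noise under any method.

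A reader might also infer that a whole-sample (standardised) odds ratio should be converted instead. At those prevalences it gives .281 to .265, further from .30, so converting it is a debatable choice of estimand and no clear improvement.

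**Conclusion.** The concern holds in a limited form. If the cluster models are fitted by unpenalised likelihood, a cluster with about 10% prevalence or less carries a material risk of no usable odds ratio: 13% to 47% of trials with 37 per arm and 5% to 30% with 53 per arm, at prevalence 10% and 5%. At 20% or more the risk is under 1% and the bias is negligible beside the sampling error, though a penalised fit is still somewhat more accurate.

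Separately, the converted d is not directly comparable with the mean-difference d of the NPI total.

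These sizes rest on an assumed prevalence range, a true benefit of .30, a latent normal score with r = .50 and the logistic conversion to d. The 53-per-arm figures treat the imputed outcomes as if they had been observed.

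**What to change.** Keep the four baseline-adjusted models and change how they are fitted and reported:

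1. Fit each model with Firth's penalised likelihood in every imputed data set before pooling the log odds ratios. Do the same in the observed-data comparison.
2. Report the odds ratio with its confidence interval, and a risk difference standardised over baseline presence.
3. If Cohen's d is kept, state the conversion formula, say that d comes from a baseline-adjusted odds ratio and is not directly comparable with the d of the NPI total, and do not carry the .33/.56 bands over to it.

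The cost is a few sentences of analysis text and standard software. No new data or participants are needed. The one drawback is that estimates are slightly shrunken towards no effect, most visibly in the rarest clusters.
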